### 2.7. Measures

A variety of tools will be used. All measures will be undertaken at baseline, at the end of the intervention, and one year after the end of the intervention (follow-up). Before the first measurement, all participants will go through a familiarisation phase to familiarise themselves with the different instruments and assessments included in this project.

a. Anthropometrics and body composition. Bodyweight and height will be assessed. Before the measurements, participants will be asked to remove their shoes, socks, and heavy clothing (coats, sweaters, coats, etc.). They will also be asked to empty their pockets and remove belts and other accessories (bands, pendants, etc.). Height will be measured using a stadiometer (Seca 22, Hamburg, Germany). This instrument must be placed on a vertical surface with the measuring scale perpendicular to the ground. Participants will be positioned in a standing position, with their shoulders balanced, and their arms relaxed along their body. Height will be taken in cm and rounded to the nearest mm. Body weight will be measured using a scale. Body weight will be recorded in kg. and the body mass index (BMI) will be determined using the formula: weight × height^2^.

b. Physical fitness. Participants will wear tracksuit bottoms and will be asked to remove accessories and any objects in their pockets. The following measures will be carried out (Figure 3): (I) agility and execution speed will be assessed through the Timed Up and Go (TUG) test, which consists of getting up from a chair, walking in a straight line three meters away, and walking back and sitting down again [25]; (II and III) postural control will be tested through a force platform (Ber-tec4060-Columbus; USA). The assessment will consist of measuring the oscillations in a static bipedal position, with eyes open (two minutes) and with eyes closed (two minutes) [26]; (IV) gait will be assessed using the mobile application “Phyphox” on the surface of the skin, at the inner edge of the tibia, to quantify the number of steps and time. Participants will be asked to walk a pre-established route, without slopes or obstacles, for 10 min, at their natural cadence and, later, walk the same route at a pace determined by complex stimuli (auditory metronome—loudspeakers, which allow for hearing beats that correspond to steps) [27]; (V) muscular endurance will be assessed by rising up from the chair or bending and straightening for 30 s, during which the strength of the lower limbs involving the vastus medialis obliquus (VMO) and the vastus lateralis (VL) will also be calculated [28]; (VI) upper limb strength will be determined by the number of times that a weight can be lifted by performing a flexion–extension of the arms for 30 s [28]; (VII and VIII) flexibility will be evaluated by two tests: “the sit and reach” for lower limb flexibility, where participants, from a seated position with one leg extended, will slowly bend down, sliding their hands down the extended leg until they touch (or pass) their toes [28]; and “the behind the back reach” test for upper limbs, assessing the shoulder’s full range of motion, which will consist of measuring with a ruler the distance between (or the overlap of) the middle fingers behind the back [28].

c. HRQoL. This will be assessed using the 36-Item Short-Form Survey (SF-36) [29] in its Portuguese version [30,31], a 36-question tool, which results in 8 dimensions of health status (physical function, physical role, bodily pain, general health, vitality, social function, emotional role, and mental health) and 2 summary components (physical and mental). Dimensions and components are scored from 0 to 100, where 0 is the worst state, and 100 is the best.

d. PAL. This will be assessed using the International Physical Activity Questionnaire Short Form (IPAQ-SF) [32]. This instrument consists of four questions informing on the frequency (days/week) and duration (minutes/day) of daily walks and activities requiring moderate to vigorous physical exertion, as well as the time (minutes/day) spent on sitting activities on weekdays and weekends. PA will be classified into three categories according to the IPAQ consensus group: sedentary (< 600 Met-minutes/week), active (≥ 600 Met-minutes/week), and very active (≥ 3000 Met-minutes/week). This instrument will be completed by the participants in its Portuguese version [33].

e. Subjective Perception of Effort. This will be assessed through the Borg Rating of Perceived Exertion Scale [34] during the sessions, consisting of 10 items for which participants rate their effort from “not at all” (1) to “maximum” (10).

f. Adherence rate. This will be controlled. For this purpose, following previous studies [35,36] the following parameters will be monitored: proportion of participants completing exercise programmes, proportion of exercise sessions attended, average number of exercise sessions completed per week, class attendance expressed as a proportion of participants reaching certain cutoffs, number of weeks in which exercise was undertaken, and proportion of days on which exercise was undertaken. In addition, recommendations from previous studies will be followed to encourage adherence to the programme, including making instructions to subjects simpler and less demanding, addressing cognitive motivational factors such as self-efficacy and health beliefs, offering social support and reinforcement, and providing reminders [37,38].

g. Level of satisfaction. This will be evaluated through the Physical Activity Enjoyment Scale (PACES) survey, which consists of 8 items that are scored from 1 to 7 points (where 1 = “I enjoy it”, 7 = “I hate it”, and 4 = “neutral”). The total score will be calculated from the sum of the items, with a maximum possible score of 56 points and a minimum of 8; the higher the score is, the greater the enjoyment is. The Portuguese version will be completed by the participants [24].

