## Abstract

Research shows that exercise training programmes lead to several improvements in older adults’ health-related quality of life (HRQoL) and well-being. This study will examine the effects of an active retirement programme on Portuguese older adults, investigating its effects on body composition, physical fitness, HRQoL, and physical activity level (PAL). Therefore, a parallel-group randomised controlled trial will be conducted, including body composition (height and body weight), physical fitness (strength, flexibility, agility, postural control, and gait), HRQoL, and PAL assessments before and after the application of the programme. The programme will be carried out for six months, two days per week (45 min), plus a year of follow-up. The programme will consist of six circuits with eight physical exercises each. The circuits will change at the end of the four weeks (one monthly circuit). The exercises’ difficulty will increase throughout the programme, with alternatives for all the participants. If the effectiveness of the programme is demonstrated, implementation in different services and municipalities could be advised, as the actors involved in health and social services should promote the well-being of their citizens through, among others, health-related physical activity and the prevention of diseases associated with inactivity.

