Research on how PA affects health-related quality of life (HRQoL) has shown that PA’s benefits regarding quality of life were limited [22,23]. Several studies have evaluated the sensorimotor system in the elderly and obtained strength, mobility, and balance improvements, but these results were not consistent due to the reduced sample [20,21], being short-term (12 weeks or less), or only assessing some abilities [17]. This study will last 24 weeks, and its effects will be measured through gait, postural control, strength, flexibility, balance, and agility. Hence, this study will aim to (1) assess the effectiveness of an active retirement programme on elderly body composition, physical fitness, HRQol, and PAL and (2) assess the programme’s effectiveness throughout the ageing process (follow-up).

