### 2.3. Sample Size

Sample size calculations were performed using the G*Power 3.1.9.4 software (Kiel University, Kiel, Germany), selecting the statistical test to compare the difference between two independent means (two groups). Thus, accepting an alpha risk of 0.05 and a beta risk of 0.2 in a bilateral contrast and assuming a moderate effect size of 0.5, a total of 160 participants (80 subjects in the experimental group and 80 in the control group) were sufficient to reach a minimum potency of 90%.

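### BMI is defined as weight multiplied by height squared instead of divided by it, so the only derived body-composition outcome would be wrong for every participant

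*Protocol article*

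**What the plan says.** Section 2.7, item a, of the protocol article covers anthropometrics and body composition. It states that "Bodyweight and height will be assessed", gives the units as "Height will be taken in cm and rounded to the nearest mm" and "Body weight will be recorded in kg", and then says that "the body mass index (BMI) will be determined using the formula: weight × height^2". The article nowhere gives a different BMI formula, a kg/m² unit or a conversion from centimetres to metres.

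Body composition is one of the outcome domains in the first aim (section 1), which is to "assess the effectiveness of an active retirement programme on elderly body composition, physical fitness, HRQol, and PAL", and it is named again in the conclusions. Only weight and height are measured for it, so BMI is the only derived quantity in that domain. Section 2.7 schedules all measures at baseline, at the end of the intervention and one year later. Section 2.8 analyses the dependent variables by repeated-measures ANCOVA adjusted for age and baseline outcome, and reports Cohen's d with a 95% confidence interval.

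**The concern.** The purpose of BMI is to express weight relative to height, and it does so by dividing by height squared. Multiplying does the opposite: the index rises with height at a given weight, and each person's weight change is multiplied by height² when it should be divided by it. If the formula were programmed as printed, every BMI value in the trial would be wrong at every visit. That includes the baseline value used as a covariate and everything reported from those values.

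The units are a second gap in the same rule. Height in centimetres, put into either the printed or the corrected formula without conversion, does not give kg/m².

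**Working it through.** **Inputs.** From section 2.7, item a: weight in kg, height in cm, index = weight × height². The article reports no BMI value, so there is no published figure to reproduce. The weights and heights below are illustrative assumptions.

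**Step 1: printed formula against BMI, height in metres.**

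| Weight, height | Printed: w × h² | BMI: w / h² |
|---|---|---|
| 75 kg, 1.60 m | 75 × 2.56 = 192.0 | 75 / 2.56 = 29.3 |
| 60 kg, 1.50 m | 60 × 2.25 = 135.0 | 60 / 2.25 = 26.7 |
| 60 kg, 1.75 m | 60 × 3.0625 = 183.8 | 60 / 3.0625 = 19.6 |

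In the last two rows, with weight equal, the taller person has the lower BMI but the higher printed index.

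**Step 2: size of the error.** The ratio of printed to true value is (w × h²) / (w / h²) = h⁴. That is 1.50⁴ = 5.1, 1.65⁴ = 7.4 and 1.80⁴ = 10.5. The ratio differs between people and equals 1 only at a height of exactly 1 m, so no participant's value is right and no single factor restores the scale.

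**Step 3: units.** With height in cm the printed formula is a further 100² = 10,000 times larger: 75 × 160² = 1,920,000. Correcting only the operator and leaving height in cm gives 75 / 160² = 0.0029.

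**Step 4: what the index would measure.** In a simulated population with height 1.62 ± 0.09 m and BMI 27.5 ± 4.5 kg/m² (assumed, independent of each other), the printed index correlates 0.79 with height and only 0.59 with true BMI.

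**Step 5: consequence for the trial comparison.** This used the same assumed population, 80 per arm, a weight-change SD of 3 kg, a programme effect of −1.5 kg, 2,000 simulated trials, and a simple ANCOVA of the post-intervention value on baseline. Height is in metres.

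| Mean over simulated trials | BMI | Printed formula |
|---|---|---|
| Adjusted difference | −0.57 | −3.93 |
| Difference / baseline SD | −0.129 | −0.074 |
| Difference / residual SD | −0.498 | −0.499 |
| t statistic | −3.14 | −3.15 |
| Power | 87% | 87% |

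The adjusted differences agree with hand calculation at the mean height: 1.62² = 2.6244, so −1.5 / 2.6244 = −0.57 and −1.5 × 2.6244 = −3.94. The sign of the effect agreed in every simulated trial.

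**The case against.** The strongest reply is that this is a slip of notation in a universally known index. A weight times height to the power −2 was perhaps intended, and a minus sign lost when the PDF was read cannot be excluded. Against that, the multiplication sign and the superscript 2 both survived, and a lost minus sign would still leave the centimetre problem. A slip is the likely origin, but this remains the only derivation the article gives, and it is wrong as it stands.

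The second reply is that a value of 192, or nearly two million with height in cm, would be noticed at once. Weight and height are recorded at each assessment, so BMI can be recomputed at any time. BMI is not an eligibility criterion, the sample size does not depend on it, and it is one of many outcomes with no primary outcome named. All of this stands, and it lowers the severity.

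The third reply is that the trial comparison is within-person over time. Adult height is nearly constant, so the direction of each person's change is preserved. Step 5 confirms this in part: the test, the power and an effect standardised by residual SD barely move. It does not rescue the raw means, the adjusted difference, or a d standardised by baseline SD, which falls from −0.129 to −0.074.

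The last reply is that unit conversion is routine and can be left to a fuller document. On its own that would be fair. Here the formula is being rewritten anyway, and naming the units costs nothing.

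**Conclusion.** The concern holds. The stated rule does not produce BMI. Applied literally, it overstates the value by height⁴, roughly 5 to 10 times between 1.50 m and 1.80 m, with people of equal weight ranked in reverse. BMI means, adjusted differences and a baseline-standardised Cohen's d would be wrong, while the ANCOVA significance test would be almost unaffected. The value-level error follows from the formula alone. The effect on the trial comparison rests on the assumed height, BMI and weight-change distributions in steps 4 and 5.

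Severity is limited: the error is probably notational, the raw data allow full recovery, and design and sample size are untouched. It should still be corrected before any BMI is derived, because it is an explicit outcome definition in the Methods.

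**What to change.** In section 2.7, item a, replace the formula with: BMI (kg/m²) = weight (kg) / [height (m)]², where height recorded in cm is divided by 100 before squaring. Check that the analysis syntax and any data-capture form that computes BMI use the same definition.

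The cost is one line of wording and one check of the code. No new data are needed, and nothing changes in the assessments, the sample size or the participants' management.

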### 2.6. Intervention

**Experimental group:** This sensorimotor training programme will be carried out for six months, twice per week. As shown in Figure 1, as the programme progresses the load will be progressively increased.

Sessions will be divided into three intensity levels: easy (no external load during the first eight weeks), intermediate (application of external load: elastic bands, shin guards, and free weights, from the 9th week to the 16th week) and advanced (increase in external load for the previous level, from the 17th week to the 24th week). Each month, a different type of session will be developed (Figure 2). Each session will last 45 min and will be divided into three phases: an initial one, consisting of a 5 min walk followed by a joint warm-up (10 min); a fundamental phase (25 min), working on exercises circuits consisting of four cycles, with eight exercises each (50 s on and 15 s off); and a return to calm with muscle stretching (10 min). Additionally, at the end of every session, the intensity will be assessed using the Borg Rating of Perceived Exertion Scale, and the level of satisfaction of the participants will be assessed employing the Physical Activity Enjoyment Scale (PACES) [24].

**Control group:** Individuals will continue with their normal daily routine, only participating in the assessments. They will be offered to perform the exercise programme when the study ends.

Moreover, to guarantee participants’ safety, different strategies will be applied:-Anamnesis of all participants;-Hygiene of the material to be used during the sessions;-Breaks between exercises;-More than one researcher assisting with the sessions;-Application of the effort scale.

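### As written, the enjoyment scale's anchors, its sum score and the stated direction of the total contradict each other, so satisfaction would be reported backwards if the text is followed literally

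*Protocol article*

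**What the plan says.** Section 2.7, item g, of the protocol article defines the satisfaction measure in four parts:

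- **Items.** The scale is one "which consists of 8 items that are scored from 1 to 7 points".
- **Anchors.** One set is given for all items: "where 1 = “I enjoy it”, 7 = “I hate it”, and 4 = “neutral".
- **Total.** "The total score will be calculated from the sum of the items", "with a maximum possible score of 56 points and a minimum of 8".
- **Direction.** "the higher the score is, the greater the enjoyment is".

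Section 2.6 says, in its description of the experimental group, that the scale is completed at the end of every session. It gives no scoring rule. Section 2.8 does not mention the scale, and reverse scoring is not mentioned anywhere in the article.

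**The concern.** The anchors run from liking to dislike, and the total is described simply as a sum. On that description a large total means dislike, yet the article reads a large total as enjoyment.

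This is a conflict between things the article does state, not a detail it leaves to a fuller document. Anyone who scored the forms from this text alone would describe a well-liked programme as disliked, or the reverse.

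Satisfaction has its own entry in section 2.7 and is collected often. Two sessions a week for 24 weeks is 2 × 24 = 48 sessions. With 80 experimental participants (section 2.3), that is up to 48 × 80 = 3,840 forms at full attendance. The Abstract and Discussion also present the programme as something that public services, associations and private centres could adopt, and whether participants liked it bears on that message.

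**Working it through.** **Inputs**, all from section 2.7, item g: 8 items; item range 1 to 7; 1 = enjoyment, 4 = neutral, 7 = hatred; total = sum of the items; higher total = more enjoyment.

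**Step 1: reproduce the stated range.** Minimum = 8 × 1 = 8. Maximum = 8 × 7 = 56. Both match the article.

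**Step 2: attach the anchors to the range, then apply the reversal that the direction sentence would need.** Reversing an item means replacing response x by 8 − x. Over eight items, the reversed total is 8 × 8 − T = 64 − T, where T is the plain sum.

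| Response to every item | Plain sum T, anchors as printed | What the direction sentence makes of T | Reversed total 64 − T |
|---|---|---|---|
| Enjoyment (1) | 8 × 1 = 8 | least enjoyment possible | 56 |
| Neutral (4) | 8 × 4 = 32 | midpoint | 32 |
| Hatred (7) | 8 × 7 = 56 | greatest enjoyment possible | 8 |

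T and 64 − T are exact mirror images (correlation −1). They agree only where T = 64 − T, that is, at T = 32.

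**Step 3: can the range show which statement is wrong?** No. It is 8 to 56 with or without reversal, so neither the stated range nor a range check on the data would expose the error.

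**Step 4: what if the printed anchors are the misprint?** Suppose the form really runs from 1 for hatred to 7 for enjoyment. The plain sum is then already right: full enjoyment gives 8 × 7 = 56. Recoding every item as 8 − x would turn that into 64 − 56 = 8 and so reverse correct data.

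**Step 5: what if the items on the form are not all anchored alike?** The article gives one anchor set, so this is an assumption. Let m items be anchored as printed and 8 − m the other way round. The plain sum for full enjoyment is m × 1 + (8 − m) × 7 = 56 − 6m. For full hatred it is m × 7 + (8 − m) × 1 = 8 + 6m.

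- m = 8: 8 for enjoyment and 56 for hatred, the case in the table.
- m = 4: 32 for both, so the plain sum cannot separate them.
- m = 0: 56 for enjoyment and 8 for hatred, as in Step 4.

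The right recode therefore depends on the form, item by item.

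**The case against.** The strongest reply is that the article never says raw responses are summed. It says only that the items are summed, and a condensed article may leave item recoding to the full protocol or to the instrument's scoring key, which is cited but not shown. On that view the study team may score the form correctly and the fault is one of wording. This stands in part: the absence of reversal is inferred from silence. A reader might infer that the trial will certainly report satisfaction backwards; the article supports that only on the condition that its text is followed literally. The reply does not remove the contradiction, because the article prints anchors, rule and direction together and nothing elsewhere in it reconciles them.

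A second reply is that little is at stake. The scale is outside the stated aims (body composition, physical fitness, quality of life and activity level) and does not enter the sample size. Control participants have no sessions to rate. This stands, and it limits the weight of the point.

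A third is that the error is recoverable, since 64 − T restores the intended total. That is true if every item is anchored as printed. If anchors differ between items, the individual responses are needed.

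A reader might also infer that any relation between enjoyment and attendance would come out with the wrong sign. The article plans no such analysis: section 2.7, item f, lists adherence proportions and averages, and section 2.8 relates neither to this scale. That consequence is not part of this point.

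**Conclusion.** The contradiction is certain and sits within one item of section 2.7. Taken literally, it inverts the satisfaction score completely: 8 and 56 change places and only 32 keeps its meaning. Which of the anchors, the scoring rule and the direction sentence is wrong cannot be settled from the article; at least one needs correcting, or a reversal step needs adding.

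The reach is narrow. It is tempting to conclude that the trial's efficacy results are affected, but the article does not support this. The only specific account of how the scale is administered is after the experimental group's sessions (section 2.6), so the scale has no control counterpart and no measurement before the sessions begin. It is therefore not a natural candidate for the group-by-time analysis in section 2.8, and no stated between-group efficacy result changes. This rests on taking section 2.6 as the operative description. The opening of section 2.7 does say that all measures are taken at baseline, at the end of the intervention and one year later, but it gives no account of how participants without sessions would rate enjoyment of them.

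The point should be corrected before satisfaction is reported. It does not threaten the main comparison.

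**What to change.** The order matters.

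1. Check the anchors item by item on the Portuguese form in use, before any recoding.
2. If the printed anchors are right, recode each item so anchored as 8 minus the response before summing. The total then runs from 8 to 56 with higher meaning more enjoyment. Alternatively, keep the plain sum and state that a lower total means more enjoyment.
3. If the anchors are misprinted, correct them in the text and leave the sum and the direction sentence unchanged.
4. State the anchors, the items reversed (if any) and the direction of the total together, so that all three agree. Keep the item responses in the data set, not only the totals.

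The cost is a look at the form, one corrected sentence and, if needed, one recode in the analysis program. Sample size, visits and the efficacy analysis are untouched.
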